### Determination of sample size

We are planning a study of independent cases and controls with 1 control per case. Superiority of bacteriophage versus placebo treatment: We assume the success rate among controls to be 0.2. If the true success rate for experimental subjects is 0.6, we will need to study 27 experimental and 27 control subjects to be able to reject the null hypothesis that the success rates for experimental and control subjects are equal with probability (power) 0.8. The type I error probability associated with this test of this null hypothesis is 0.05.

Non-inferiority of bacteriophage versus antibiotic treatment: We assume the success rate among subjects receiving bacteriophage treatment to be 0.6 and we accept a non-inferiority margin of 0.35. If the true success rate for experimental subjects is 0.95, we will need to study 27 experimental subjects and 27 control subjects to be able to remain within the non-inferiority margin with a probability (power) 0.8. The type I error probability associated with this test of this alternative hypothesis is 0.05. We will use a continuity-corrected chi-squared statistic or Fisher’s exact test to evaluate these hypotheses.

Thus, we will include 27 patients per treatment group, i.e. 81 patients in total. Withdrawn patients will be replaced.

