### Investigations

The patients planned for transurethral resection of the prostate with a positive urine culture (≥10^4^ colony forming units/mL) of predefined uropathogens sensitive to Pyo bacteriophage (i.e. Enterococcus spp., *Escherichia coli*, Proteus mirabilis, Pseudomonas aeruginosa, Staphylococcus spp., and Streptococcus spp.) and fulfilling the study inclusion criteria will be included into the study after providing written informed consent. The patients will be assessed using bladder and pain diary [18] and an IPSS questionnaire [19]. The Fig. 1 gives an overview of the procedures that patients will undergo during the study.

After inclusion, patients will be randomized in a double-blind fashion to the study treatment arms in a 1:1:1 ratio. Patients of all study arms will undergo monopolar transurethral resection of the prostate and insertion of a suprapubic catheter if not already present. Study arm a) will receive bacteriophage solution (Pyo bacteriophage) and study arm b) placebo solution (sterile bacteriology media). Either solution will consist of 20 mL and will have an identical appearance for both the bacteriophage and the placebo, respectively. An investigator not involved in the assessment of the clinical outcome will deliver the solution and teach the patient / health care provider how to instill the solution into the bladder. The solution will be instilled using the suprapubic catheter, 2 times per 24 h (i.e. 8.00, 20.00) for 7 days, starting the first day after surgery. The patients will be asked to retain the solution in the bladder for approximately 30–60 min. No antibiotic prophylaxes will be given to the study treatment arms a and b.

Study arm c) will receive an antibiotic treatment according to the antibiotic sensitivity pattern and common clinical practice.

At the end of treatment (i.e. after 7 days) or at withdrawal / drop out, urinalysis, urine culture, bladder and pain diary [18] and an IPSS questionnaire [19] will be taken. Patients with persistent UTIs will undergo antibiotic treatment according to antibiotic sensitivity for 7 days.

Drop out criteria for patients in the study arm a and b are fever >38 °C, CRP >100 mg/L, other clinical signs or symptoms for a systemic infection or withdraw from the patients. These patients will undergo antibiotic treatment according to antibiotic sensitivity.

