### Study outcome measures

Primary: Success of intravesical treatment, defined as normalization of urine culture (no evidence of bacteria, i.e. <10^4^ colony forming units/mL) after 7 days of bacteriophage, placebo, or antibiotic treatment.

Secondary: Adverse events, in categorization according to the National Cancer Institute Common Terminology Criteria for Adverse Events (CTCAE) version 4 in grade 1 to 5 (http://ctep.cancer.gov/protocolDevelopment/electronic_applications/ctc.htm) during treatment phase.

Tertiary: a) Changes in bladder and pain diary assessment of number of voids, number of leakages, post void residual, pain assessment using a visual analog scale (0 (no pain) to 10 (strongest possible pain)), b) IPSS items at baseline versus day 7 under intravesical bacteriophage, placebo, or antibiotic treatment.

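### Unlimited replacement of withdrawn patients, with infection-based drop-out criteria in arms a and b only, can take failures out of those arms and tilt the non-inferiority comparison towards bacteriophage

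*Protocol article*

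**What the plan says.** Under Determination of sample size the article states: "Thus, we will include 27 patients per treatment group, i.e. 81 patients in total". The next sentence is "Withdrawn patients will be replaced". It gives no reason, time window or arm to which this is limited.

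Under Investigations: "Drop out criteria for patients in the study arm a and b are fever" above 38 °C and CRP above 100 mg/L, and the list goes on to "other clinical signs or symptoms for a systemic infection or withdraw from the patients". For those who meet a criterion, "These patients will undergo antibiotic treatment according to antibiotic sensitivity". No corresponding criteria are given for arm c, the open-label antibiotic arm.

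The same section schedules the final assessments "At the end of treatment (i.e. after 7 days) or at withdrawal / drop out, urinalysis, urine culture" included. The primary outcome under Study outcome measures is a urine culture below 10^4 CFU/mL "after 7 days of bacteriophage, placebo, or antibiotic treatment".

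**The concern.** Three of the four drop-out criteria describe the infection getting worse. The fever and CRP thresholds are also exclusion criteria in Table 1, so a patient who reaches them in the trial has changed since entry. Such a patient moves to antibiotics and cannot supply a day-7 culture on the allocated solution alone.

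If that patient is swapped for a new one and leaves the analysis, arms a and b are selected on something that happened after randomisation and is related to outcome. Arm c has no equivalent infection exit. At stake is a false claim that bacteriophage is non-inferior to antibiotics, one of the two hypotheses stated in the Background. The comparison with placebo also ceases to be one between the groups as randomised.

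**Working it through.** **Inputs from Determination of sample size.** Placebo success 0.20; bacteriophage 0.60; 0.95 in the non-inferiority paragraph, read here as the antibiotic rate; margin 0.35; n = 27 per group; type I error 0.05; power 0.80; Fisher's exact or continuity-corrected chi-squared test.

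**Assumed, because the article gives no figure.** A share q of an arm's randomised patients drops out and is replaced, and the replaced patients leave the analysis. Arm c has no drop-outs.

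**1. The plan's own figure.** For 0.20 v 0.60, two-sided 0.05 and power 0.80, the normal approximation gives 23 per group, or 28 with continuity correction. Full enumeration of the two-sided Fisher test at 27 per group gives power 0.802. The stated 27 is reproduced to within one patient.

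**2. Apparent rate in arm a.** Let s be the share of drop-outs whose culture would have been a success. The rate among those kept is

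(0.60 − q·s) / (1 − q).

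This exceeds 0.60 whenever s is below 0.60.

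**3. False non-inferiority.** The true difference is put at the margin: 0.60 − 0.95 = −0.35. The probability of declaring non-inferiority is enumerated at n = 27 with the Newcombe lower bound.

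All drop-outs are culture failures (s = 0):

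| q | apparent rate, arm a | one-sided 0.025 | one-sided 0.05 |
|---|---|---|---|
| 0 | 0.600 | 0.032 | 0.062 |
| 5% | 0.60/0.95 = 0.632 | 0.061 | 0.109 |
| 10% | 0.60/0.90 = 0.667 | 0.113 | 0.190 |
| 15% | 0.60/0.85 = 0.706 | 0.206 | 0.318 |
| 20% | 0.60/0.80 = 0.750 | 0.359 | 0.503 |

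A simple Wald bound at one-sided 0.025 gives much the same: 0.029, 0.057, 0.111, 0.210 and 0.376.

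Half of the drop-outs are culture successes (s = 0.5), one-sided 0.025:

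- q = 10%: (0.60 − 0.05)/0.90 = 0.611, probability 0.041.
- q = 20%: (0.60 − 0.10)/0.80 = 0.625, probability 0.054.

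**4. Bacteriophage v placebo** (s = 0 in both arms, Fisher, two-sided 0.05, true rates 0.60 and 0.20):

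| q in a | q in b | apparent rates | apparent difference | power |
|---|---|---|---|---|
| 0 | 0 | 0.60 v 0.20 | 0.40 | 0.80 |
| 0 | 20% | 0.60 v 0.25 | 0.35 | 0.65 |
| 10% | 20% | 0.667 v 0.25 | 0.417 | 0.81 |
| 20% | 20% | 0.75 v 0.25 | 0.50 | 0.94 |

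The apparent difference can fall below or rise above the true 0.40.

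**The case against.** The strongest reply is that the article never says replaced patients are excluded. A culture is taken at drop-out, which is compatible with keeping their outcomes, and analysis sets are commonly left to a fuller document. This stands in part: the bias is conditional on exclusion, and a plan that keeps every randomised patient would remove it. But the replacement rule is stated here and is unrestricted. Topping up to 27 with a day-7 on-treatment endpoint points to the replaced patients not being counted.

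Withdrawn could also mean only patients who choose to leave. That is possible, since the Safety section speaks separately of withdrawal of consent. Yet Investigations lists the patient's own withdrawal among the drop-out criteria and pairs the two terms when scheduling assessments, so the wider reading is the natural one.

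A reader might infer more than the documents support:

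- That every drop-out is a treatment failure. The fourth criterion covers patients who leave for any reason, and the endpoint is purely microbiological, so some drop-outs may have a culture below the threshold.
- That arm c keeps all of its failures. The replacement sentence covers all three groups; only the infection criteria are confined to a and b.
- That both comparisons are biased in a known direction. Against placebo, the direction depends on the drop-out rates in the two arms.
- That a false non-inferiority rate near 0.36 is to be expected. It is the upper end of an assumed range.

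Finally, the Newcombe bound and the one-sided 0.025 level are choices made for this check. The article names Fisher or chi-squared tests at 0.05. The pattern is the same at one-sided 0.05 and with the Wald bound.

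**Conclusion.** The point holds in conditional form. As written, the replacement rule allows infection-related failures to be swapped out of arms a and b, and nothing shown keeps them in the analysis. If they leave it, and fewer than 60% of arm a drop-outs would have had a successful culture, the non-inferiority comparison is biased towards bacteriophage.

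With none lost from arm c and a true difference at the margin, the error at one-sided 0.025 goes from 0.03 to between 0.04 and 0.11 at 10% drop-out, and to between 0.05 and 0.36 at 20%. The lower figure in each pair takes half of the drop-outs as culture failures, the upper takes all. In the all-failure case 5% drop-out, one or two patients, roughly doubles the error. For bacteriophage against placebo, randomisation is broken in the same way but no direction can be given: power runs from 0.65 to 0.94 over the scenarios shown, against 0.80 planned. Because a stated rule can produce a false claim on a main hypothesis and the correction is cheap, it should be made before the data are analysed.

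**What to change.** - Delete the replacement sentence, or limit replacement to patients withdrawn before randomisation.
- State that every randomised patient is analysed in the assigned arm.
- In the primary analysis, count as a failure, identically in all three arms, any patient who drops out for infection, starts non-assigned antibiotics before the day-7 culture, or has no day-7 culture.
- Use the culture taken at drop-out in a sensitivity analysis.
- Repeat the non-inferiority analysis per protocol.

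This is an analysis rule only and alters no clinical drop-out or treatment criterion. It does widen the meaning of failure beyond the culture result, which is why the culture-based sensitivity analysis belongs beside it.

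The cost is protocol wording. Patients who leave for unrelated reasons count as failures, which slightly lowers the observed success rates and power. If infection drop-outs are already counted as failures in the planning rates of 0.60 and 0.20, those rates, the 27 per group and the exact power of 0.80 are unchanged.

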### Investigations

The patients planned for transurethral resection of the prostate with a positive urine culture (≥10^4^ colony forming units/mL) of predefined uropathogens sensitive to Pyo bacteriophage (i.e. Enterococcus spp., *Escherichia coli*, Proteus mirabilis, Pseudomonas aeruginosa, Staphylococcus spp., and Streptococcus spp.) and fulfilling the study inclusion criteria will be included into the study after providing written informed consent. The patients will be assessed using bladder and pain diary [18] and an IPSS questionnaire [19]. The Fig. 1 gives an overview of the procedures that patients will undergo during the study.

After inclusion, patients will be randomized in a double-blind fashion to the study treatment arms in a 1:1:1 ratio. Patients of all study arms will undergo monopolar transurethral resection of the prostate and insertion of a suprapubic catheter if not already present. Study arm a) will receive bacteriophage solution (Pyo bacteriophage) and study arm b) placebo solution (sterile bacteriology media). Either solution will consist of 20 mL and will have an identical appearance for both the bacteriophage and the placebo, respectively. An investigator not involved in the assessment of the clinical outcome will deliver the solution and teach the patient / health care provider how to instill the solution into the bladder. The solution will be instilled using the suprapubic catheter, 2 times per 24 h (i.e. 8.00, 20.00) for 7 days, starting the first day after surgery. The patients will be asked to retain the solution in the bladder for approximately 30–60 min. No antibiotic prophylaxes will be given to the study treatment arms a and b.

Study arm c) will receive an antibiotic treatment according to the antibiotic sensitivity pattern and common clinical practice.

At the end of treatment (i.e. after 7 days) or at withdrawal / drop out, urinalysis, urine culture, bladder and pain diary [18] and an IPSS questionnaire [19] will be taken. Patients with persistent UTIs will undergo antibiotic treatment according to antibiotic sensitivity for 7 days.

Drop out criteria for patients in the study arm a and b are fever >38 °C, CRP >100 mg/L, other clinical signs or symptoms for a systemic infection or withdraw from the patients. These patients will undergo antibiotic treatment according to antibiotic sensitivity.

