## Methods and design

### Study design

This study is a randomized, placebo-controlled, double-blind trial investigating bacteriophages in UTI treatment. The study is conducted at the Tzulukidze National Center of Urology (TNCU), Tbilisi, Georgia. Phage preparations (i.e. Pyo bacteriophage solution: commercially available and registered in Georgia) and continuous adaption cycles during the course of the study, to enhance the treatment effect, are done at the Eliava Institute of Bacteriophages, Microbiology, and Virology in Tbilisi (EIBMV), Georgia.

Figure 1 gives an overview of the procedures. Patients planned for transurethral resection of the prostate are screened for UTIs at the TNCU. Urine cultures including antibiotic sensitivity testing are performed in a duplicate manner. If eligible microorganisms which would potentially match with the type of bacteriophage present in Pyo bacteriophage (5 components: Enterococcus spp., *Escherichia coli*, Proteus mirabilis, Pseudomonas aeruginosa, Staphylococcus spp., and Streptococcus spp.) are detected, urine cultures are then sent for bacteriophage sensitivity testing to the EIBMV (Fig. 2) [12]. In case of a positive in-vitro sensitivity testing, concluded within 24 h after receipt of the urine culture, patients will be asked for study participation. After written informed consent, patients are randomized in a double-blind fashion to the study treatment arms in a 1:1:1 ratio to receive either: a) Pyo bacteriophage solution, b) placebo (sterile bacteriology media with identical color as treatment arm a), or c) antibiotic treatment according to the antibiotic sensitivity pattern, respectively. Treatment arms a and b will be double-blind but treatment arm c, i.e. the control arm representing common clinical practice, is open label. All treatments are intended for 7 days starting at the day of surgery (arm c) or one day thereafter (arm a and b). Prior and at the end of treatment (i.e. after 7 days) or at withdrawal / drop out, urinalysis, urine culture, bladder and pain diary [18] and an International Prostate Symptom Score (IPSS) questionnaire [19] will be taken. Patients with persistent bacteriuria will undergo antibiotic treatment according to antibiotic sensitivity.

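### Clinical drop-out is defined for arms a and b only, so a bacteriophage patient who fails clinically may be scored on an early culture or replaced, with no such exit stated for the antibiotic arm

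*Protocol article*

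**What the plan says.** Four statements in the protocol article bear on this point.

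- **Exit rule (Investigations).** "Drop out criteria for patients in the study arm a and b are fever >38 °C, CRP >100 mg/L", followed by other signs of systemic infection and withdrawal by the patient. Then: "These patients will undergo antibiotic treatment according to antibiotic sensitivity".
- **Arm c (Investigations and Study design).** "Study arm c) will receive an antibiotic treatment according to the antibiotic sensitivity pattern and common clinical practice". The design section says that "treatment arm c, i.e. the control arm representing common clinical practice, is open label". No fever, CRP or systemic-infection exit is stated for this arm.
- **Timing of the culture (Investigations).** It is taken when the 7 days of treatment end, "or at withdrawal / drop out, urinalysis, urine culture, bladder and pain diary".
- **Endpoint and replacement.** Under Study outcome measures, success is a urine culture below 10^4 colony forming units/mL "after 7 days of bacteriophage, placebo, or antibiotic treatment". Fever, CRP and systemic infection are not part of it. Determination of sample size says: "Withdrawn patients will be replaced".

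**The concern.** Non-inferiority of bacteriophage to antibiotic treatment is one of the trial's two stated hypotheses, with a margin of 35 percentage points. Patients in every arm have a monopolar resection and a suprapubic catheter, so postoperative fever or systemic infection can occur in any of them. In arm a such an event ends study treatment and brings the culture forward. In arm c no corresponding rule is stated.

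A patient who needs rescue has failed bacteriophage treatment in the clinical sense. Yet a culture taken at drop-out may fall below the threshold and be counted as a success. If the replacement sentence covers clinical drop-outs, the patient may leave the denominator altogether. Either route can change the arm a rate for reasons unrelated to how well the treatment works, and the arm c rate is not exposed to the same route. With 27 patients per arm, one or two patients handled differently are visible in the result.

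**Working it through.** **The plan's own figures.** The article gives no event rate and no drop-out allowance, so there is no figure on this point to reproduce. The stated 27 per arm comes out at 28 for 0.2 v 0.6 (two-sided 5%, power 0.8, continuity-corrected). That is close enough, and the point does not depend on it.

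**The rules side by side**

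| Question | Arms a and b | Arm c |
|---|---|---|
| Fever, CRP or systemic infection | Drop-out, then rescue antibiotics | No rule stated |
| Culture used | Day 7, or earlier at drop-out | Day 7, or at withdrawal/drop-out, with no clinical criteria given |
| Replaced? | If 'withdrawn' includes clinical drop-outs | Same sentence, but no clinical drop-out is defined |
| Event part of the endpoint? | No | No |

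Whether replacement reaches clinical drop-outs is ambiguous. Elsewhere the article writes withdrawal and drop-out as two terms, but the exit rule lists patient withdrawal as one of the drop-out criteria.

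**Inputs for the illustration**

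- Arm a success rate of 0.60 and 27 patients per arm: Determination of sample size.
- e, the share of arm a patients who meet the clinical criteria: not in the document; assumed 5% and 10%.
- q, the share of those patients whose culture at drop-out is below the threshold: not in the document; assumed 0.2 to 0.6, borrowing the planned placebo and bacteriophage rates as a range.
- Reference: 0.60 is read as the rate among all randomised patients with these events counted as non-success.

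**Replacement.** The rate becomes 0.60/(1 − e).

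- e = 5%: 0.60/0.95 = 0.632
- e = 10%: 0.60/0.90 = 0.667

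In patients, 27 × 0.60 = 16.2 expected successes becomes 27 × 0.632 = 17.1 or 27 × 0.667 = 18.0. The expected number of drop-outs among 27 is 27 × 0.05 = 1.35 or 27 × 0.10 = 2.7.

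**Early-culture scoring.** The rate becomes 0.60 + q × e.

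- e = 5%: 0.61 (q = 0.2) to 0.63 (q = 0.6)
- e = 10%: 0.62 to 0.66

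**The opposite direction.** Suppose the target is the day-7 culture alone, and s is the success rate these patients would have had on it (again assumed 0.2 to 0.6). Counting them as non-success in arm a only then lowers arm a by s × e. That is 1 to 3 points at 5% and 2 to 6 points at 10%. As shares of the 35-point margin, 0.01/0.35 to 0.03/0.35 is 3% to 9%, and 0.02/0.35 to 0.06/0.35 is 6% to 17%.

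The sign of the shift therefore depends on a scoring choice that the text leaves open. No a-versus-c difference is computed here, because the article gives no event rate for arm c and attaches the 0.95 to experimental subjects.

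**The case against.** The strongest reply has three parts.

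1. **The rule is about care.** Arms a and b receive no antibiotic and need a rescue rule; arm c is already on sensitivity-guided antibiotics. This is right and justifies different care. It does not settle how the patient is counted.

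2. **Scoring of drop-outs belongs in the full protocol or SAP.** In part this stands: the article's silence on scoring would not be a finding by itself. But the article does state an exit limited to two arms, a culture taken at that exit, and replacement of withdrawn patients. Those statements together allow the early-culture and replacement readings.

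3. **The arm c half is inferred.** This also stands. A reader might conclude that a febrile antibiotic patient is kept on treatment and scored as a day-7 success. The article does not say so. It provides for a culture at withdrawal or drop-out without limiting it to arms a and b, and it leaves arm c to usual practice. All that can be said is that no such exit is stated for arm c.

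A reader might also infer that the comparison with placebo is distorted by the one-sided rule. It is not, because arms a and b share the rule. Replacement could affect that comparison too, but that is a question about the replacement sentence.

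**Conclusion.** The point holds in a limited form. Stated rules allow a clinically failing bacteriophage patient to be scored on an early culture or replaced, and no matching exit is stated for the antibiotic arm. Direction and size cannot be determined from the document. The figures of 0.63 and 0.67 for arm a are illustrations. They rest on assumed event rates of 5% and 10%, on 'withdrawn' including clinical drop-outs, and on 0.60 being the rate with these events counted as failures.

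Two stronger readings are tempting and not supported. One is that the antibiotic-minus-bacteriophage difference would shrink from 0.35 to 0.28 at a 10% event rate. That holds arm c at 0.95 without allowing for the same events there. The other pushes the event rate to 20%, where arm a would reach 0.60/0.80 = 0.75; nothing in the article supports a rate that high.

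The choice should still be fixed before the data are seen, because the correction is small and the comparison concerned is one of the two stated hypotheses.

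**What to change.** Leave clinical care unchanged, and add the following to Determination of sample size and Study outcome measures.

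- Every randomised patient stays in the primary analysis. Patients are not replaced after a clinical drop-out.
- A patient in arm a or b who meets the clinical drop-out criteria after the first instillation, or who starts rescue antibiotics before the day-7 culture, is a non-success. Counting the criteria from the first instillation matters because arms a and b start the day after surgery, so early postoperative fever alone should not count against a treatment not yet given.
- The culture remains the primary endpoint in arm c.
- A sensitivity analysis also counts as non-success, in arm c, the same events recorded as adverse events, or a change of antibiotic for lack of effect. Adverse events are already a secondary outcome, so this needs no new schedule of assessments.

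**Cost.** The success rate in arms a and b falls slightly: by the s × e shown above for arm a if 0.60 was meant as a culture-only rate, and not at all if it already counts these patients as failures. The primary comparison with antibiotics becomes conservative, because clinical events count against arm a but not arm c; the sensitivity analysis shows how much that matters. Making fever and CRP part of the primary endpoint in all three arms would be more symmetric. It would also bring clinical judgement in an open-label arm, and fever of non-urinary origin, into an objective endpoint. That trade-off is debatable and is not needed to close this gap.
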